# 7 Ethical Considerations

---

## 7.1 Risks

---

### Delayed Antipsychotic Administration

---

According to the guidelines of the National Institute for Health and Care Excellence (NICE Clinical Guideline CG 178) for psychosis and schizophrenia in adults: prevention and management, after the initial evaluation by the psychiatrist, 7 days are typically allowed before the initiation of medication to finalize the diagnosis with the treatment team and discuss treatment options with the patient and their family.

For this research project, the administration of antipsychotic medication (AP) may be delayed by an additional 2-3 days to perform the "BEFORE" imaging. The team will always aim to schedule

appointments within the 7-day period; however, if there are limitations (holidays, participant availability, equipment malfunctions, etc.), these additional 2-3 days will be considered while ensuring that the risk associated with this prescription delay remains minimal.

The risks associated with delaying the prescription of AP will be evaluated on a case-by-case basis in collaboration with the patients according to their clinical condition. Any patient who wishes for immediate AP prescription will receive it and will not be eligible for this research project. The majority of patients request additional time themselves to reflect and research the medications before receiving the prescription. Most request the medication introduction at the next appointment, 2 weeks later, and everything proceeds correctly without side effects, based on clinical experience related to the 2-week delay without AP.

The patient is free to change their mind during this period, either to accelerate the start of AP or to refuse AP altogether. In such cases, the patient will be excluded from the study. Additionally, as provided for in the usual care model of the PEP, the patient will be seen once or twice a week by their primary clinician from the PEP clinic for support and guidance towards non-pharmacological approaches for managing stress and psychotic symptoms. In case of an emergency, the patient is advised to contact their primary clinician. Should a change in health status occur during this period, appropriate medical follow-up will be conducted, and if the need for earlier medication initiation arises, the participant will simply be excluded from the study.

---

### Blood Sampling

The risks associated with blood sampling and the installation of a glucose monitor are the same as those for all standard blood draws, including bleeding, bruising, discomfort, dizziness, pain at the sampling site, and the possibility of infection.

---

### MRI

Magnetic resonance imaging (MRI) is completely painless. It is a radiation-free examination. No particular consequences for humans have been described. The only risks are related to implanted pacemakers, heart valves, or any unreported metallic foreign bodies. A detailed and standardized questionnaire is conducted by the technologist to ensure the absence of metallic bodies. Claustrophobic individuals may feel uncomfortable, experience anxiety, or have a panic attack.

---

### Radiation Exposure

For the entire study, the effective dosimetry received by the participant for the entire imaging process will be a maximum of 11.6 mSv, including a 40% safety factor. These effective doses are below the annual threshold limit of 20 mSv set and authorized by CHUS for the participation of healthy subjects in research projects involving radiation. For more details, see the attached document from the CHUS Radiation Protection Officer ([name]): "Radiation Protection Note and Dose Calculation."

---

## 7.2 Benefits

It is possible that the participant may benefit personally from their participation in the research project, but this cannot be guaranteed. This study will contribute to knowledge in psychiatry, particularly metabolic psychiatry.

### 7.3 Compensation

---

Participants will receive compensation of CAD 60 for visits V0, V1, and V3, and CAD 100 for visits V2 and V4 (a total of 5 visits, amounting to CAD 380) given in cash at each visit, as well as taxi or parking vouchers for their transportation.

### 7.4 Information and Consent Form

---

Before undertaking any procedures directly related to the research project, the participant's consent will be obtained through an information and consent form. This form aims to inform the patient about the study in simple and familiar terms. The participant will have all the necessary time to read it and receive satisfactory answers to their questions. A person will always be available for this purpose. This process aims to obtain free and informed consent. Given the potentially more vulnerable status of participants, their understanding of the study and consent will be validated throughout the project. The accompanying person will also be consulted on this matter.

### 7.5 Voluntary Participation

---

The participant is free to participate in the research project and to terminate their participation at any time without any impact on the quality of care and services to which they are entitled, or on relationships with the responsible researchers, their treating physician, or other professionals. In case of withdrawal, the participant's well-being and safety will be ensured by study termination and follow-up procedures according to the circumstances at the time. The disclosure of any new information and modifications to the original protocol that may challenge the participant's decision to continue their participation will be communicated. The responsible researchers may also terminate the participant's participation in the research without their consent if it is in the participant's best interest or if they do not adhere to the project's guidelines.

### 7.6 Significant Incidental Findings

---

Following the various tests and examinations in the project, it is possible that significant previously unknown anomalies may be identified that are important for the participant's health. In such a case, the participant will be informed, and one of the project's referring physicians will ensure appropriate medical follow-up. It is possible that they will contact the family doctor or other specialists to ensure the participant is properly taken care of. An incidental finding could exclude the participant from the project.

### 7.7 Confidentiality

---

All information collected during this study will be treated with the utmost confidentiality. All collected samples and data will be de-identified. The key will be kept electronically separate from other project data and held by the principal investigator. [name], the psychiatrist from the PEP team and the project's referring physician, is also the principal investigator of this research project. However, he will only have access to certain anonymized data, notably brain imaging and PET results. Access to information stored on computers is restricted by using a password and firewall. Any data used in future publications will be anonymous so that no data specific to the different study participants will allow them to be identified as individuals.

The consent form clearly mentions the individuals who will or may have access to the information related to this research, namely the principal researchers, associated researchers, their collaborators, and, more rarely, representatives of the research ethics committee. All these individuals are subject to confidentiality rules. Authorization for the reuse of data and biological samples will be requested from participants. Research data may thus be used in other studies on brain metabolism approved by the CIUSSS de l'Estrie - CHUS Research Ethics Board. Therefore, data will be kept by the principal investigators. Given their conservation period, biological samples will be stored for a maximum of 10 years and then destroyed securely.

Participants will be informed that some brain imaging data or "scan images" may be used in scientific publications. The "scan images" obtained after image processing are data reconstructed from algorithms and do not allow re-identification of the persons.

### 7.8 Storage of Samples and Data

---

Given their conservation period, de-identified biological samples will be stored at -80°C in a restricted access freezer at the Research Center on Aging (CDRV) for a maximum of 10 years, then destroyed securely according to institutional procedures.

Data collected during the study will be stored on the Research Center on Aging's computer system.

Participants are identified in the computer system by a code. No other personal information that could identify the participants is present, except for the date of birth. Some de-identified paper source documents (questionnaires, blood test results, etc.) will be stored in the participant's file in locked filing cabinets. These cabinets are located in restricted-access offices at the CDRV.

Data will be stored for 25 years. PET scan data will be stored in accordance with Health Canada's policy.

### 7.9 Insurance

---

All involved researchers and physicians are covered by professional liability insurance.

### 7.10 Clinical Trial Registration

---

To reduce bias and meet publication requirements, this study will be registered in the public registry [[www.clinicaltrial.gov](http://www.clinicaltrial.gov)](<https://clinicaltrial.gov>).

### 7.11 Study Limitations

---

Several limitations emerge from this pilot study. We have tried to minimize or measure potential confounders and biases within the constraints of a first pilot study.

#### *Diagnostic Variability:*

The participants included in the study will likely have different final diagnoses. The PEP clinic model is transdiagnostic, meaning a patient is admitted for a "first episode of psychosis," but the final diagnosis may vary between psychosis NOS (Not Otherwise Specified), chronic psychosis, brief psychotic disorder, schizophreniform disorder, schizophrenia, bipolar disorder, personality disorder, or delusional disorder. The PEP clinic's objective is to provide services to all these patients. We have chosen not to exclude

these sub-pathologies or other comorbidities. This will be a limitation of the study, as the different pathologies may present different metabolic profiles or responses, but we believe that metabolic disturbances are common across these pathologies.

*Antipsychotic Type and Dose Variability:*

We also chose not to exclude participants based on the type of AP used for treatment or the chosen dose, which may not correspond to the standard effective dose according to the literature, because the PEP clinic's approach is based on clinical evaluation rather than theory, and the study is intended to reflect real-world conditions. Therefore, the determination of this dose is done with the patient and varies for each patient. It is possible that the dose or type (or change) of AP may have a different impact on metabolism. Given the small sample size, it will not be possible to create subgroups. This should be addressed in a future study. A dose equivalency table will be used retrospectively to determine the number of participants with theoretically effective doses, but some variability is possible and would be a limitation of the study.

*Adherence to Treatment:*

Similarly, adherence to treatment is another concern. We have included an adherence questionnaire to try to control this parameter, but self-reported instruments have their own limitations. Particularly, verifying medication intake is challenging in psychiatric illnesses. Plasma AP levels could be considered in a future study.

*Substance Use as a Confounder:*

Drug, alcohol, or concomitant medication use is another confounding factor, presenting a limitation to the study. We have planned questionnaires to document it, but self-reported instruments also have limitations.

*Nutritional and Lifestyle Factors:*

The impact of dietary habits and potential follow-up with a nutritionist or dietitian, or even following a "diet" independently, could introduce variations in the study. It would be interesting to evaluate spontaneous dietary changes in a future study, as they are known to occur with AP use.

*Control Group Limitations:*

The control group will be drawn from a database of healthy participants obtained in the past 10 years and characterized as metabolically healthy. They may not be representative of the current general population. A control group in a future study would be relevant.

*Continuous Glucose Monitoring:*

Data obtained by continuous glucose monitoring will likely be more informative than standard plasma measurements, but in this exploratory study, we propose making this part optional to obtain at least preliminary exploratory results and assess the acceptability and feasibility for guidance in a future study.

---

## **8 Variables and analysis**

---

### **8.1 Analyses**

All data will be compiled, and differences BEFORE vs. AFTER for the various measurement variables will be assessed using Wilcoxon signed-rank non-parametric tests for paired data.

Correlations will also be performed, particularly between brain function (variables related to global and regional changes in cerebral energy metabolism), blood levels of various measured parameters, and scores from clinical questionnaires (global psychopathology, functioning, depression, cognition, etc.).

In a second phase, comparisons will be made with a control group from a brain imaging database conducted in age-matched participants without the condition (Project 08-111 [name]).

The significance threshold will be set at  $p < 0.05$ . All statistical analyses will be performed using SPSS 24.0 software (SPSS Inc, Chicago, USA).

As this clinical study includes an exploratory component, new analyses or complementary analyses may be added based on the literature or preliminary analyses.

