### Blood Sampling During PET

---

For each PET exam, plasma fractions will be separated by centrifugation, and plasma radioactivity will be immediately counted using a scintillation counter to evaluate the radiotracer's blood kinetics. Plasma will then be used to measure glucose and ketones (for tracer uptake calculations).

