### ***Primary variables related to changes in cerebral energy metabolism:***

- Cerebral metabolic rate of glucose ( $\mu\text{mol}/100 \text{ g}/\text{min}$ ) quantified with 18F-FDG;
- Net glucose influx with 18F-FDG ( $\text{Kglu}; \text{min}^{-1}$ );
- Cerebral metabolic rate of acetoacetate with 11C-AcAc ( $\mu\text{mol}/100 \text{ g}/\text{min}$ );

- Net acetoacetate influx with 18F-FDG (Kglu; min).

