**Secondary variables related to systemic metabolism:**

- Plasma glucose concentrations (mM);
- Plasma insulin concentrations (pM);
- Plasma HbA1c concentration (%);
- HOMA-IR score.

**Secondary variables related to changes in cerebral energy metabolism in a healthy control group matched by age and sex ([name] database):**

- Cerebral metabolic rate of glucose ( $\mu\text{mol}/100 \text{ g/min}$ ) quantified with 18F-FDG;
- Net glucose influx with 18F-FDG (Kglu; min);
- Cerebral metabolic rate of acetoacetate with 11C-AcAc ( $\mu\text{mol}/100 \text{ g/min}$ );
- Net acetoacetate influx with 18F-FDG (Kglu; min).

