**Exploratory variables related to metabolic and systemic changes:**

- Plasma concentrations of total ketones (mM);
- Plasma concentrations of triglycerides, total cholesterol, and free fatty acids (mM);
- Laboratory analysis parameters: Complete blood count, renal function (creatinine), liver function (AST, albumin), thyroid function (TSH), inflammation marker (C-reactive protein);
- Physical measurements (weight, height, waist circumference, blood pressure);
- Metabolomics;
- Cytokine and inflammatory profiles (plasma concentration).

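### Section 8.1 lets a cerebral metabolic rate be tested against the plasma substrate used to calculate it, so glucose-with-glucose and acetoacetate-with-ketones correlations can reach p < 0.05 through the shared term

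*Protocol*

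**What the plan says.** Section 8.1 of the protocol plans correlations "between brain function (variables related to global and regional changes in cerebral energy metabolism), blood levels of various measured parameters", together with clinical questionnaire scores. It names no pairs, no correlation coefficient and no blood draw. One threshold covers all tests: "The significance threshold will be set at" p < 0.05.

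Section 8.2 lists two kinds of primary brain variable:
- metabolic rates in µmol/100 g/min: "Cerebral metabolic rate of glucose" and "Cerebral metabolic rate of acetoacetate with 11C-AcAc";
- influx constants in min⁻¹, such as "Net glucose influx with 18F-FDG" and a corresponding constant for acetoacetate.

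The same section lists plasma glucose (mM) and HOMA-IR as secondary systemic variables, and plasma total ketones (mM) as exploratory.

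Section 6.6, on blood sampling during PET, gives the purpose of the scan-time plasma: "Plasma will then be used to measure glucose and ketones (for tracer uptake calculations".

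The clinical blood panel is a different sample. It is drawn at V1 and V3 after a 12-hour fast, whereas the PET visits V2 and V4 require a 4-hour fast (section 6.4).

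**The concern.** A rate obtained as an uptake constant multiplied by a plasma concentration contains that concentration. Correlating the rate with the concentration correlates a product with one of its own factors. Even when the uptake constant has nothing to do with plasma level, the expected correlation is above zero, so the ordinary test of no association does not test whether uptake capacity varies with plasma level.

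The false discovery rate correction planned for imaging data addresses the number of tests, not a null hypothesis that is already off zero. The limitations in section 7.11 do not mention the shared term. At stake is an association between brain and blood fuel measures, strongest for ketones, being read as a biological finding when the calculation alone could produce it.

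**Working it through.** **Inputs from the protocol.** Ten completers (section 5.1); threshold 0.05 (section 8.1), taken as two-sided; rates in µmol/100 g/min and influx constants in min⁻¹ (section 8.2); scan-time plasma used in the uptake calculation (section 6.6). There is no stated power or error figure for these correlations to reproduce.

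**Assumptions.** The protocol does not write out the formula. The units differ by a concentration, and section 6.6 supplies that concentration, so I take rate = K × C up to a constant, where C is the plasma substrate. All coefficients of variation (CVs) are assumed and shown as a range. Total ketones are treated as the value entering the acetoacetate rate; if only acetoacetate enters, the overlap is partial and the result lies nearer the separate-draw case below.

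**Induced correlation.** With K and C independent and log-normal, the correlation of log rate with log C is

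sd(log C) / √[sd(log K)² + sd(log C)²], where sd(log X) = √ln(1 + CV²).

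- Glucose, CV of K 15%, CV of C 10%: sd(log K) = √ln(1.0225) = 0.149; sd(log C) = √ln(1.01) = 0.100; correlation = 0.100 / √(0.0223 + 0.0100) = 0.56.
- Ketones, CV of K 30%, CV of C 40%: sd(log K) = √ln(1.09) = 0.294; sd(log C) = √ln(1.16) = 0.385; correlation = 0.385 / √(0.0862 + 0.1484) = 0.80.

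At n = 10 the critical correlation is 0.632, so the ketone example is expected to lie beyond it and the glucose example close to it.

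**Rejection rates by simulation.** n = 10, Spearman test of BEFORE-to-AFTER changes, K independent of C, correlation 0.5 between visits for each, PET-visit plasma on both sides:

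| Pair | CV of K | CV of plasma | Rejection at 0.05 |
|---|---|---|---|
| Glucose | 20% | 5% | about 10% |
| Glucose | 15% | 10% | about 35% |
| Glucose | 10% | 10% | about 58% |
| Ketones | 30% | 50% | about 83% |
| Ketones | 20% | 80% | about 98% |

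Over K CVs of 10 to 20% and glucose CVs of 5 to 10%, the range is about 10 to 60%. Over K CVs of 20 to 30% and ketone CVs of 30 to 80%, it is about 58 to 98%. Replacing the rate by K gives 5 to 6% throughout.

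**Separate draw.** If the blood level comes from V1/V3, and correlates 0.5 to 0.7 with the PET-visit value, rejection falls to about 6 to 28% for glucose and 11 to 48% for ketones. At 0.7, the 15%/10% glucose case gives about 14 to 17% and the 30%/50% ketone case about 27 to 38%. The spread depends on whether the difference between draws persists from one visit to the next.

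**The opposite null.** If the rate, not K, is independent of plasma level, then K = rate / C carries the shared term. K against its own substrate then rejects 34% (rate CV 15%, glucose 10%), 72% (30%, ketones 50%) and 85% (20%, ketones 80%), with negative correlations, and the rate is clean.

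**The case against.** Section 8.1 names no pairs, and choosing them is commonly left to an analysis plan. The influx constants are already primary variables, so correlations with K are within the plan. This stands in part: the protocol permits the problem pairs without prescribing them. But it fixes the variables and the threshold and excludes nothing, so carrying it out as written includes them.

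The listed blood variables match the panel in section 6.6 that is drawn at V1/V3, so the same measurement need not sit on both axes. This stands, and it is why the smaller range is given. It also means HOMA-IR is touched only indirectly: insulin appears only in that panel, not among the analytes measured in PET plasma.

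The null is open to choice. Section 3 reports that raising plasma ketones can increase the brain's fuel supply, so a rate that rises with ketones may be a real effect of interest. This stands too. It argues for stating the question, since neither variable is clean under both nulls.

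A reader might infer that secondary objective 1 is invalidated. The protocol does not support that: the objective names continuous glucose monitoring as its systemic measure, and that does not enter the PET calculation. Nor does the argument reach insulin, lipids, cytokines or C-reactive protein.

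**Conclusion.** The point holds for two pairs: glucose metabolic rate with plasma glucose, and acetoacetate metabolic rate with plasma ketones. If K is independent of plasma level, the nominal 5% test at n = 10 rejects about 10 to 60% of the time for glucose and 58 to 98% for ketones with the PET-visit plasma. With the V1/V3 draw the figures are about 6 to 28% and 11 to 48%. They rest on rate = K × C, on assumed CVs, and on assumed between-draw correlations of 0.5 to 0.7.

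Two stronger readings should be resisted. One is that every correlation between brain and blood is compromised; only a rate against its own substrate is directly affected. The other is that K is always the safe choice; it is so only when the question is whether uptake capacity varies with plasma level. The consequence is limited to the blood-level correlations in 8.1 of a small pilot, but it could mislead there and is easily avoided.

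**What to change.** In section 8.1:
- State which blood draw, PET-visit or V1/V3, supplies the plasma values for the correlations.
- For a tracer's own substrate, base the test on the influx constant, and say that the question is whether uptake capacity varies with plasma level.
- Show the metabolic rate against its own substrate beside it as descriptive, without a p-value, noting that the two share a term.
- Keep the metabolic rates for all other correlations, such as symptom scores, cognition and C-reactive protein.

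In section 8.2, correct the acetoacetate influx constant. Both the primary list and the control-group list attach it to 18F-FDG and the symbol Kglu, and the ketone part of the fix relies on it.

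The cost is a few sentences and no new data, since the influx constants are already planned primary variables. The downside is small: there is no p-value for a rate against its own substrate, and a correlation of K with substrate must be read as a change in the uptake constant, not in total fuel supply.
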